### Qualitative data collection

Qualitative process data will be collected to describe how the intervention unfolds in practice and to assess the reliability of implementing the intervention across sites. The MDETs will be asked to record field notes of their experiences with the intervention, including their collaborations with PCPs, in a reflective journal. Quarterly debriefing sessions with the MDETs to discuss implementation issues that arise during the intervention period will be recorded, transcribed and analyzed for emergent themes, such as communication, shared decision making and so on.

In addition, purposively selected patients
[44], MDET educators and PCPs will be asked to participate in a 45- to 60-minute open-ended qualitative face-to-face or telephone interview after 12 months from the start of the intervention. Potential participants will be stratified by sites, then invited to participate in an interview in order to ensure representation from all sites involved in the trial (maximum variation sampling)
[45]. To obtain saturation for a heterogeneous group, interviews are planned with 15 to 20 people representing each group of patients, PCPs and educators who have participated in the MDET intervention. We will interview participants until saturation has been achieved (that is, when no new themes are being generated). Patient interview questions will pertain to how useful the intervention was in terms of better understanding their condition, diabetes self-management strategies, and the convenience and quality of delivery. Both MDETs and PCPs will be asked questions about their experiences with the intervention, their collaboration and teamwork, barriers and facilitators to implementation, and suggestions to improve the intervention. Participants will be compensated for their time. All interview questions will be piloted on two patients, PCPs and diabetes educators prior to interviews.

### Statistical analysis

All sites will eventually receive the MDET intervention on an ongoing basis following the stepped wedge design, which allows us to evaluate the intervention effect utilizing both within- and between-site information while controlling for underlying time trends (for example, Hussey *et al.*, 2007)
[46]. We plan to sample 20 unique patients/charts per site per time period (1,200 in total), based on the primary hypothesis of a greater proportion of patients reaching the clinically recommended target (HbA1C ≤7%). The proposed sample size will give rise to over 80% power at a significance level of 1% (adjusting for multiple testing) assuming the between-site variation in terms of the coefficient of variation is 0.8. The minimal detectable effect size (expressed as a relative risk) based on the proposed sample is as small as 18%, for baseline proportions “p” in the range of 0.3 to 0.6 (as reported in McCrate *et al.*, 2010
[47], Harris *et al.*, 2005
[7] and Borgermans *et al.*, 2009
[15]]. For example, considering a conservative baseline proportion of *P* = 0.5 and an intraclass correlation (correlation between patients from the same site) of 0.39, we will have 80% power to detect a relative change in proportion of 18% (that is, from 0.5 to 0.59 ((0.59 to 0.5)/0.5 = 0.09/0.5 = 0.18)) attributed to the intervention over a six-month period. We will assess the sample size at the end of the 12 months, and if necessary, the sample size estimation will be adjusted according to established methods described in Chen *et al.* 2004
[48].

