**Methods/design:**

This study will use a non-blinded, cluster-randomized controlled trial stepped wedge design to evaluate the Mobile Diabetes Education Teams' intervention in improving patient clinical and care process outcomes. A total of 1,200 patient charts at participating primary care sites will be reviewed for data extraction. Eligible patients will be those aged ≥18, who have type 2 diabetes and a hemoglobin A1c (HbA1c) of ≥8%. Clusters (that is, primary care sites) will be randomized to the intervention and control group using a block randomization procedure within practice size as the blocking factor. A stepped wedge design will be used to sequentially roll out the intervention so that all clusters eventually receive the intervention. The time at which each cluster begins the intervention is randomized to one of the four roll out periods (0, 6, 12, and 18 months). Clusters that are randomized into the intervention later will act as the control for those receiving the intervention earlier. The primary outcome measure will be the difference in the proportion of patients who achieve the recommended HbA1c target of ≤7% between intervention and control groups. Qualitative work (in-depth interviews with primary care physicians, MDET educators and patients; and MDET educators’ field notes and debriefing sessions) will be undertaken to assess the implementation process and effectiveness of the MDET intervention.

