## Background

Diabetes mellitus is a chronic illness that requires a lifelong commitment to complex lifestyle modifications involving nutrition management, a physically active lifestyle, regular self-monitoring of blood glucose and adherence to medications and/or insulin therapy. Proper management of these lifestyle modifications have been shown to reduce the risk and progression of diabetes complications
[1-6]. Achieving and sustaining effective management is challenging; more than half of those living with diabetes in Canada are unable to meet the recommended target for glycemic control (≤7% hemoglobin A1c (HbA1c))
[7]. As a result, diabetes self-management support (DSMS) is recommended by Canadian clinical practice guidelines for the management of diabetes as a valuable resource that supports and teaches patients the skills to actively participate in the management of their illness
[8].

DSMS is a collaborative process through which people with, or at risk for, diabetes gain the knowledge and skills needed to modify behavior and successfully self-manage the disease and its related conditions. It is an interactive, ongoing process involving the person with diabetes (and possibly the caregiver and/or family) and a diabetes educator(s), and focuses on essential self-care behaviors, such as healthy eating, being active, monitoring blood glucose, taking medication, problem solving, healthy coping and reducing risks of further complications
[9]. DSMS primarily relies on patients and diabetes educators to define management issues, set priorities, establish collaborative goals, identify barriers, create a management plan and problem-solve to maintain optimal management
[10,11]. The few studies that exist on the delivery of DSMS in primary care have found that DSMS has numerous benefits on patient clinical and care process outcomes, such as an improvement in patient knowledge
[12-14]; a reduction in body weight
[13], HbA1c
[12-16], cholesterol
[14-17], fasting blood glucose
[13,18], self-blood glucose monitoring
[16] and blood pressure
[18]; and improved primary care physician (PCP) adherence to diabetes clinical practice guidelines
[14,17]. However, none of these studies have been conducted within a Canadian setting.

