### Participants

The study involves two groups of participants: PCPs and patients assigned to their care. PCPs will be selected if they agree to refer patients with type 2 diabetes to the MDET. Patients will be included if they are ≥18 years of age, have type 2 diabetes and have an HbA1c of ≥8%. Patients who are newly diagnosed or have lived with the disease for many years are eligible because the primary treatment/management goal is to achieve glycemic control and other clinical targets to reduce the risk of complications. As such, we plan to include both prevalent and incident cases, but restrict inclusion only to patients who are at high risk (≥8%) in our research sample. Patients who have a type of diabetes that requires intense and specialized treatment, such as type 1 diabetes, gestational diabetes or patients on a complex multiple daily insulin regime, will be excluded. Ethical approval for this study has been granted by the Ryerson University Research Ethics Board, including the waiver of consent to review patient medical charts. Informed consent for all other data collection activities will be gained from all participants.

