### Quantitative data collection

A repeated cross-sectional survey of patients’ medical charts will be carried out at all sites at five time intervals (0, 6, 12, 18 and 24 months). This survey entails randomly selecting charts of eligible patients who received primary care at the participating site at the time of the survey. This results in different patients being included at the five time points. Therefore, data on the demographic and clinical profile of patients will be obtained and controlled statistically prior to performing outcome comparisons between study groups. In the control sites, a 12-month retrospective data extraction will also be performed for each patient chart selected. In the intervention sites, a 12-month retrospective data extraction will be performed prior to the start of the intervention and up to 12 months during the intervention for each patient chart selected. This will be conducted to assess changes in patient care processes and clinical outcomes.

Data will be collected on:

1. Baseline demographic and clinical information (that is, age, sex, duration of diabetes, smoking status, comorbidity);

2. Treatment modality (that is, diet, oral agents, insulin, or insulin with oral agents), medical treatment, duration of insulin therapy;

3. Frequency and outcomes of tests or measures of HbA1c, LDL-C, TC-HDL; high density lipoprotein (HDL-C), diastolic and systolic blood pressure, glomerular filtration rate (eGFR), albumin/creatinine ratio (ACR), waist circumference, and weight.

The data will be extracted from patient charts for baseline comparisons between randomized clusters. For our primary hypothesis, we will collect HbA1c to assess the proportion of patients who achieve the recommended target for HbA1c (that is, HbA1C ≤7%) and assess change within patients in the intervention and between cluster groups. For our secondary hypothesis we will collect LDL-C, TC-HDL, and diastolic and systolic blood pressure to assess achievement of each of the recommended clinical targets (LDL-C <2.0 mmol/L, TC-HDL ratio < 4.0 and blood pressure <130/80 mmHg) and assess change within patients in the intervention and between cluster groups.

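### The power statement assumes 30% to 60% of patients are already at HbA1c 7% or less, but the trial samples only patients with HbA1c of 8% or more

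*Protocol article*

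**What the plan says.** - **Outcome.** The Abstract (Methods/design) defines the primary outcome as the "difference in the proportion of patients who achieve the recommended HbA1c target of ≤7% between intervention and control groups".
- **Who is sampled.** The Participants section states: "Patients will be included if they are ≥18 years of age, have type 2 diabetes and have an HbA1c of ≥8" percent. It adds that the plan is to "restrict inclusion only to patients who are at high risk (≥8%) in our research sample". Quantitative data collection describes each of the five surveys as "randomly selecting charts of eligible patients who received primary care at the participating site at the time of the survey", so the restriction applies to every chart.
- **Planning proportion.** The Statistical analysis section takes baseline proportions at target "in the range of 0.3 to 0.6" from three references (7, 15 and 47). Its worked example reads "considering a conservative baseline proportion of" 0.5, with an intraclass correlation of 0.39. It claims 80% power at the 1% level for a relative change of 18%, from 0.50 to 0.59.
- **Where one source comes from.** The Background cites reference 7 for the statement that "more than half of those living with diabetes in Canada are unable to meet the recommended target for glycemic control".
- **Safeguard.** The Statistical analysis section says the sample size will be assessed at 12 months and adjusted if necessary.

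**The concern.** A patient whose qualifying HbA1c is 8% or more is not at 7% or less on that reading. A baseline proportion at target of 30% to 60% therefore does not describe the patients whose charts will be drawn. It resembles the figure the Background gives for people with diabetes in general, and the article makes no adjustment for the entry floor.

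The plan states its detectable effect as a relative change, so the planning proportion matters directly. Eighteen percent of 0.5 is 9 points; eighteen percent of 0.10 is 1.8 points. A reader who takes the 18% figure at face value would believe the trial can detect an effect that, in the sampled population, may be far below its resolution.

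**Working it through.** **Inputs from the article.** 20 charts per site per period, 1,200 in total, five time points; hence 1,200 / (20 × 5) = 12 sites, three in each of the four Table 3 sequences. Coefficient of variation 0.8, significance level 1%. Sidedness is not stated; two-sided is assumed.

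**Input not in the article.** The control proportion at 7% or less among patients who entered at 8% or more. Assumed range: 0.05 to 0.20.

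**Formula.** Stepped-wedge (Hussey-Hughes) variance with fixed period effects:

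Var = I·σ²·(σ² + T·τ²) / [(I·U − W)·σ² + (U² + I·T·U − T·W − I·V)·τ²]

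Here I = 12, T = 5, σ² = p(1 − p)/20 and τ = 0.8p. From Table 3:
- U = 3 × (5 + 4 + 3 + 2) = 42
- W = 3² + 6² + 9² + 12² + 12² = 414
- V = 3 × (25 + 16 + 9 + 4) = 162
- I·U − W = 90
- U² + I·T·U − T·W − I·V = 1,764 + 2,520 − 2,070 − 1,944 = 270

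Power = Φ(δ/SE − 2.576). The detectable difference at 80% power is (2.576 + 0.842) × SE = 3.417 × SE after rounding.

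**The plan's own example, p = 0.5.** σ² = 0.0125 and τ² = 0.16. The intraclass correlation reproduces: 0.16 / (0.16 + 0.25) = 0.39. Var = 0.15 × 0.8125 / (1.125 + 43.2) = 0.00275, so SE = 0.0524. For 0.50 to 0.59, power = Φ(0.09/0.0524 − 2.576) = 19.5%, not 80%. The detectable difference is 17.9 points, or 36% relative. A schedule with a true pre-intervention baseline gives the same result. This shortfall is a separate problem; it is shown because 36%, not the stated 18%, is the benchmark for the effect of changing p.

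**Lower control proportions, same formula.** For p = 0.10: σ² = 0.0045, τ² = 0.0064, Var = 0.054 × 0.0365 / (0.405 + 1.728) = 0.000924, SE = 0.0304.

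| p | SE | 18% relative, in points | Power | Detectable difference, points | Relative | Power for 9 points |
|---|---|---|---|---|---|---|
| 0.05 | 0.0214 | 0.9 | 1.6% | 7.3 | 146% | 95% |
| 0.10 | 0.0304 | 1.8 | 2.4% | 10.4 | 104% | 65% |
| 0.20 | 0.0414 | 3.6 | 4.4% | 14.1 | 71% | 34% |
| 0.50 | 0.0524 | 9.0 | 19.5% | 17.9 | 36% | 19.5% |

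**Sensitivity.** Dropping the period effects, the most favourable variant, lifts power for 18% relative only to 2.4% to 9.4% over p = 0.05 to 0.20. The table uses the variance at the control proportion. Averaging p(1 − p) over both proportions gives detectable differences of 12.4 points (124%) at p = 0.10 and 15.5 points (78%) at p = 0.20, and power for 9 points of 76%, 50% and 30% at p = 0.05, 0.10 and 0.20.

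**The word *conservative*.** Within the plan's own range, power for 18% relative is 7% at p = 0.3 and 32% at p = 0.6. The value 0.5 is therefore not the cautious end for a relative effect. It is the cautious choice for an absolute difference: the detectable differences at 0.3, 0.4, 0.5 and 0.6 are 16.3, 17.5, 17.9 and 17.6 points.

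**The case against.** **Scale.** The primary outcome is a difference in proportions, and the worked example can be read as a 9-point gain. On that reading a lower control rate helps: power rises from 20% at p = 0.5 to 65% at p = 0.10. This stands. A reader might infer that the wrong planning proportion simply means less power, or that the stated effect is meaningless in this population. Neither follows. The loss applies to the relative effect, which is how the plan expresses its detectable effect size.

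**The later control rate.** Charts are followed for up to 12 months, newly diagnosed patients are eligible, and those on complex multiple daily insulin regimes are excluded. Some control patients may well reach 7% or less after qualifying. This also stands. A reader might infer that the control rate must be 0, or at most 0.20; the article settles neither. It rules out 0.3 to 0.6 only on the qualifying reading, and offers no support for that range afterwards.

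**Sources.** It is tempting to say that all three references describe unselected patients. Only reference 7 can be shown from the article to concern people with diabetes in general. The HbA1c selection in references 15 and 47 is not described.

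**Attribution.** Setting 104% or 71% against the stated 18% would charge two errors to one cause. The part due to the planning proportion is the move from 36% to 71% or more.

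**Reassessment at 12 months.** It could limit the harm, but the article does not say that the baseline proportion will be revised.

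**Conclusion.** The concern holds in this form: the power statement rests on a baseline proportion at target that contradicts the entry criterion, and the article gives no ground for applying it to the restricted sample under usual care.

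If the control rate is 0.05 to 0.20, power for an 18% relative change is about 2% to 4%, and the detectable difference is about 7 to 14 points (146% to 71% relative). The plan's own 0.5 gives 20% power and 18 points (36% relative). Calling 0.5 *conservative* is wrong for the relative effect the plan states.

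These sizes rest on 12 sites, a coefficient of variation of 0.8 held constant as p falls, a two-sided 1% test, and the assumed control range. At p = 0.05 a 20-chart cell expects one patient at target (20 × 0.05), so the normal approximation is weak there. The contradiction itself needs none of these assumptions.

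**What to change.** 1. Re-base the calculation on the control proportion at 7% or less among patients previously at 8% or more. Estimate it from the month-0 charts and their 12-month retrospective extraction, using patients with a reading of 8% or more early in that window.
2. State the detectable effect as an absolute difference, with its relative equivalent, over a range of control proportions such as 0.05, 0.10 and 0.20.
3. Delete the 0.3 to 0.6 range and the word *conservative*.
4. Use the re-based proportion in the 12-month sample size reassessment that is already planned.

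The cost is rewording and a re-run of the power formula on data that will be extracted anyway. The downside is a less favourable stated relative effect. Changing p alone does not repair the 80% claim, which fails on the plan's own inputs and needs its own correction.

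### On the relative-risk scale used for sizing, a baseline of 0.5 is not conservative, and one 18% detectable effect cannot hold for baselines from 0.3 to 0.6

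*Protocol article*

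**What the plan says.** The Statistical analysis section of the protocol article plans 20 charts per site per survey, 1,200 in all. It assumes a between-site coefficient of variation (CV) of 0.8 and claims "over 80% power at a significance level of 1% (adjusting for multiple testing"). It states that the minimal detectable effect, as a relative risk, "is as small as 18%, for baseline proportions “p” in the range of 0.3 to 0.6". The one worked case is introduced by "considering a conservative baseline proportion of *P* = 0.5", with an intraclass correlation (ICC) of 0.39 and 80% power for a change "from 0.5 to 0.59". No calculation is shown at any other baseline. The same section plans to reassess the sample size at 12 months.

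The Background remarks that "more than half of those living with diabetes in Canada are unable to meet the recommended target for glycemic control", citing one of the three sources later used for the sizing range.

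**The concern.** The binomial variance p(1−p) peaks at p = 0.5, so 0.5 is the cautious choice when the target is a fixed absolute difference. The plan's target is relative. An 18% relative change is 0.09 at p = 0.5 but only 0.054 at p = 0.3. The signal therefore falls by 40%, while the variance falls only from 0.25 to 0.21. Power for the stated effect is lower at 0.3 than at 0.5, so the word conservative points the wrong way and a single figure cannot describe the range.

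At stake is a sizing statement that readers will rely on, and the 12-month reassessment. If 0.5 is carried forward as the cautious value, a lower observed control rate could be taken as reassuring when it means less power for the stated relative effect.

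**Working it through.** **Inputs.** From Statistical analysis: significance level 1% (sidedness not stated; two-sided assumed), CV 0.8, ICC 0.39, 20 charts per site per survey, 1,200 in total. From Quantitative data collection: five cross-sectional surveys. From Table 3: four start times. Derived: 1,200/(20 × 5) = 12 sites, taken as 3 per start time. From Quantitative data analysis: time as a fixed effect, site as a random effect.

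**Consistency of CV and ICC.** At p = 0.5, τ = 0.8 × 0.5 = 0.40, so ICC = 0.16/(0.16 + 0.25) = 0.390. This agrees with the plan.

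**The plan's 80% at 0.5.** The Hussey–Hughes variance is

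Var = Iσ²(σ² + Tτ²) / [(IU − W)σ² + (U² + ITU − TW − IV)τ²], with σ² = p(1−p)/20.

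For I = 12, T = 5 and Table 3 as coded, U = 42, W = 414 and V = 162. The two bracketed design terms are then 90 and 270.

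- p = 0.5: σ² = 0.0125, τ² = 0.16. Var = 0.121875/44.325 = 0.00275, SE = 0.0524. Power = Φ(0.09/0.0524 − 2.576) = Φ(−0.86) ≈ 19.5%.
- p = 0.3: σ² = 0.0105, τ² = 0.0576. Var = 0.037611/16.497 = 0.00228, SE = 0.0477. Power = Φ(0.054/0.0477 − 2.576) ≈ 7.4%.

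The same calculation gives 12.1% at 0.4 and 31.7% at 0.6. The relative change detectable with 80% power is (2.576 + 0.842) × SE/p: about 54%, 44%, 36% and 29% at 0.3, 0.4, 0.5 and 0.6. If Time 1 of the first group is coded as control, as the Table 3 footnote implies, power at 0.5 is 14.8%. A one-sided 1% test with Table 3 as coded gives 27.1%. Even 600 against 600 independent patients give 71%. No variant tried at the 1% level reaches 80% at p = 0.5, so the plan's figure is not reproduced.

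**The range error, with the 80% accepted.** Let z = 2.576 + 0.842 = 3.417 at p = 0.5. For a fixed 18% relative change, the signal-to-noise ratio relative to p = 0.5 is

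r(p) = [0.18p/√(p(1−p))] / [0.09/√0.25] = √(p/(1−p)).

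Power = Φ(3.417·r − 2.576), and the detectable relative change = 0.18/r.

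| Baseline | r | Power for 18% relative | Relative change at 80% power |
|---|---|---|---|
| 0.3 | 0.655 | 36.7% | 27.5% |
| 0.4 | 0.816 | 58.5% | 22% |
| 0.5 | 1 | 80% | 18% |
| 0.6 | 1.225 | 94.6% | 14.7% |

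The full stepped-wedge variance with CV 0.8, rescaled to 80% at 0.5, gives 37.3%, 58.8%, 80% and 94.5%, with detectable changes of 27.3%, 22%, 18% and 14.7%. Other anchored variants give between 34% and 45% at 0.3 (both-arm variance 34%, one-sided 1% 40%, two-sided 5% 45%). In every variant power rises with the baseline.

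**Absolute scale.** Under the stated inputs the detectable absolute difference is 3.417 × SE: 0.163, 0.175, 0.179 and 0.176 at 0.3, 0.4, 0.5 and 0.6. It is largest at 0.5, so the label conservative would be right on that scale.

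**The case against.** **The wording may name a best case.** The detectable effect is given as small as 18%, which in ordinary use is the smallest value in the range and no guarantee at every baseline; the 80% is tied to 0.50 against 0.59. This is a fair reading, but it does not rescue the figure. If 18% holds at 0.5, the smallest value in the range is about 15%, at 0.6. The label conservative stays wrong on either reading.

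**The 37% is not this trial's power.** This stands. A reader might infer that power falls from 80% to 37% as the control rate drops. The documents do not support that, because the starting 80% does not follow from their own inputs. The anchored figures measure the inconsistency within the statement and must not become replacement values.

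**The control rate may be only just below 0.5.** This also stands. A reader might infer from the Background that a lower rate is documented. It says only that more than half miss the target, so 0.49 would fit, where anchored power is still about 78%. It also concerns people living with diabetes in general, whereas Participants restricts the sample to HbA1c of 8% or more. No usable baseline rate can be taken from it.

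**The consequence is limited.** A reader might infer that a null result would be taken to exclude an 18% improvement. The plan reports confidence intervals at the 1% error level, and those would govern the interpretation, so that inference is not supported. The effect on the 12-month reassessment remains.

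**Conclusion.** The point holds as an error in the stated range and in the word conservative. On the relative scale 0.3 is the hard case, and no reading of the single 18% fits 0.3 to 0.6. The direction rests on p/(1−p) rising with p and did not change in any variant tried.

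Conditional on the plan's 80% at 0.5 and a two-sided 1% test, the error is a drop to about 37% power at 0.3, or a detectable change of about 27% instead of 18%. Unconditionally, with 12 sites inferred and equally divided among start times, the stated inputs give about 20% power at 0.5 and 7% at 0.3, with detectable relative changes of about 36% and 54%. The failure of the 80% to reproduce is a separate and larger problem. Correcting it at 0.5 alone would leave this one in place.

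**What to change.** In the Statistical analysis section:

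- Delete the word conservative for P = 0.5.
- Replace the single 18% with the detectable relative change at each of 0.3, 0.4, 0.5 and 0.6. Recompute these from the stated stepped-wedge inputs, with the number of sites and the sidedness of the test written out. Do not scale them from the 80%.
- Make the figure at the low end of the range the headline. Alternatively, state the effect as an absolute difference, for which 0.5 is the conservative value.
- Apply the same reasoning in the 12-month sample-size check, so that a lower observed control rate is recognised as lower power for a given relative effect.
- Do not adopt a specific baseline rate from the source cited in the Background.

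The cost is a revised paragraph and a four-row table, and the published figures become less favourable. Correcting the statement needs no extra charts; whether the trial is large enough is a separate question raised by the unreproduced 80%.

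### At P = 0.5 the between-site CV of 0.8 and the ICC of 0.39 contradict each other, and the stated 80% power for 0.50 to 0.59 follows from neither

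*Protocol article*

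**What the plan says.** All the inputs are in the Protocol article. The first six come from Statistical analysis and the last from Quantitative data collection.

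- Between-site spread: "assuming the between-site variation in terms of the coefficient of variation is 0.8".
- Worked example: "considering a conservative baseline proportion of *P* = 0.5", together with "an intraclass correlation (correlation between patients from the same site) of 0.39".
- Result claimed for that example: "80% power to detect a relative change in proportion of 18" per cent, that is, from 0.50 to 0.59.
- General claim: "over 80% power at a significance level of 1% (adjusting for multiple testing").
- Detectable relative change as small as 18% for baseline proportions "in the range of 0.3 to 0.6".
- Sample: "We plan to sample 20 unique patients/charts per site per time period (1,200 in total").
- Surveys: charts are drawn "at all sites at five time intervals (0, 6, 12, 18 and 24 months").

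The outcome is binary (HbA1c at or below 7%). The power statement refers to the usual stepped-wedge linear model with a random site effect and fixed time effects. The article gives neither a residual variance nor a number of sites, and does not say whether the test is one- or two-sided.

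**The concern.** A binary outcome with mean p has total variance p(1-p). Once the between-site part is chosen, the within-site part is fixed. The CV and the ICC are therefore two expressions of one quantity, and at a given p only one of them can be chosen freely. Here both are given at P = 0.5, and they differ.

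This matters because a stepped wedge compares each site largely with itself, so the standard error is driven by the within-site variance. That variance is 0.25, 0.1525 or 0.09 depending on how the two figures are read.

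The stake is whether 1,200 charts can detect the planned nine-point difference. The article also plans to reassess the sample size at 12 months, and that step needs a variance model that holds together.

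**Working it through.** **1. Reproducing the ICC.** At P = 0.5, CV 0.8 gives a between-site SD of 0.8 x 0.5 = 0.4 and a variance of 0.16.

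- The stated value comes back as 0.16/(0.16 + 0.25) = 0.390. This adds the between-site variance to the full Bernoulli variance, for a total of 0.41.
- The total for a yes/no outcome at 0.5 is 0.25. The correlation between two patients of one site is then 0.16/0.25 = 0.64, with within-site variance 0.25 - 0.16 = 0.09.
- Keeping ICC 0.39 instead gives between-site variance 0.39 x 0.25 = 0.0975, CV = sqrt(0.0975)/0.5 = 0.62 and within-site variance 0.1525.
- Reading 0.39 as an ICC on the latent logistic scale does not reconcile the pair; it gives a CV of about 0.53.

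**2. Trying to reproduce the 80%.** Assumptions: 1,200/(20 x 5) = 12 sites, three per sequence, and Table 3 as printed. The variance of the intervention effect is

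Var = I s (s + T t) / [(I U - W) s + (U² + I T U - T W - I V) t]

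where t is the between-site variance and s the within-site variance divided by 20. Here I = 12, T = 5, U = 42, W = 414 and V = 162, so

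- I U - W = 504 - 414 = 90
- U² + I T U - T W - I V = 1764 + 2520 - 2070 - 1944 = 270

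For the pair as stated, s = 0.25/20 = 0.0125 and t = 0.16. Then Var = 0.15 x 0.8125/(1.125 + 43.2) = 0.00275 and SE = 0.0524. A direct generalised least squares calculation gives the same SE.

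Power is Phi(0.09/SE - z), with z = 2.576 (two-sided 1%) or 2.326 (one-sided 1%). The detectable change at 80% power is (2.576 + 0.842) x SE.

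| Reading at P = 0.5 | Between | Within | SE | Power, two-sided | Power, one-sided | Detectable change, two-sided |
|---|---|---|---|---|---|---|
| Pair as stated | 0.16 | 0.25 | 0.0524 | 19.5% | 27.1% | 0.179 |
| CV 0.8, consistent | 0.16 | 0.09 | 0.0316 | 60.9% | 70.0% | 0.108 |
| ICC 0.39, consistent | 0.0975 | 0.1525 | 0.0410 | 35.3% | 44.9% | 0.140 |

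No row reaches 80%, and no row gives a detectable change of 0.09.

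**3. What would give 80%.** A within-site variance of 0.0625 gives s = 0.003125, SE 0.0263, two-sided power 80.06% and a detectable change of 0.0899. That variance is 0.25 squared, as if p(1-p) had been entered as an SD. The same s arises from variance 0.25 with 80 charts per site per survey (0.25/80), four times the planned number.

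**4. The range 0.3 to 0.6.** CV 0.8 is held and total variance kept at p(1-p). The target is an 18% relative change, tested two-sided at 1%.

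| p | Between | Within | ICC | Difference sought | SE | Power |
|---|---|---|---|---|---|---|
| 0.3 | 0.0576 | 0.1524 | 0.27 | 0.054 | 0.0408 | 10.5% |
| 0.4 | 0.1024 | 0.1376 | 0.43 | 0.072 | 0.0389 | 23% |
| 0.5 | 0.16 | 0.09 | 0.64 | 0.09 | 0.0316 | 61% |
| 0.6 | 0.2304 | 0.0096 | 0.96 | 0.108 | 0.0103 | nearly 100% |

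The last row is an artefact. The between-site SD is 0.48 against a possible maximum of sqrt(0.24) = 0.49, which means sites where almost all or almost no patients are at target.

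**The case against.** Five points can be made for the plan.

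- **The two figures are one number written two ways.** In the linear planning model it is common to enter p(1-p) as the residual variance beside the between-site variance, and 0.39 follows from 0.8 in that way. This explains the origin of the 0.39. It is a fair approximation when the between-site part is small, but here that part is 64% of the total. The article also defines its ICC in words as a between-patient correlation, and 0.39 is not that correlation at CV 0.8.
- **The pair is not impossible for binary data in general.** This is correct. With ICC = CV² p/(1-p), both hold at p = 0.39/(0.64 + 0.39) = 0.38, inside the stated range. The contradiction is at P = 0.5, the only proportion for which an ICC is given.
- **The inconsistency is conservative.** This is also correct. A total of 0.41 overstates the noise, and repairing it raises power from about 20% to 35% or 61%. A reader might infer that the impossible total variance produced the 80%. The figures do not support that, because the total of 0.41 gives about 20%.
- **"As small as" 18% could mean the best case in the range.** Even so, the article's own example claims exactly 18% at P = 0.5, and the claim fails there.
- **The final analysis does not use these inputs, and a reassessment is planned.** The mixed-model analysis is indeed unaffected. The power statement is still wrong as printed, and the 12-month reassessment needs a coherent starting point.

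A reader might also conclude that p(1-p) was entered as an SD by mistake. The match at 80.06% suggests this, but the article gives no residual variance and so does not prove it.

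**Conclusion.** The point holds in two separate parts.

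First, at P = 0.5 the stated CV and ICC are incompatible for a yes/no outcome: 0.8 goes with 0.64, and 0.39 goes with 0.62.

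Second, and more important, the stated 80% power and 18% detectable change do not follow from 1,200 charts under either input. Two-sided power is 20% to 61%. The choice between the two stated inputs, each taken consistently, moves it from 35% to 61%, a factor of 1.7. With the pair as stated, the detectable change is about 0.18 (36% relative), twice the 0.09 claimed. The first fault does not explain the second.

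The power figures rest on 12 sites and equal allocation, both derived or assumed here, and on the cited linear model with Table 3 as printed. One-sided testing does not rescue the claim. The incompatibility of CV and ICC needs none of these assumptions.

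**What to change.** Rewrite the sample-size paragraph as follows.

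- State one variance input and derive the other: between-site variance = ICC x p(1-p), and within-site variance = p(1-p) minus that.
- Drop the constant CV of 0.8 over baseline proportions of 0.3 to 0.6.
- State the number of sites, the allocation per sequence and whether the test is one- or two-sided.
- Restate power and detectable difference for 1,200 charts over a range of ICC values.
- Use the same variance model in the sample-size reassessment already planned at 12 months.

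The cost is a recalculation and one rewritten paragraph. The stated power will become less favourable, and the team may have to accept a larger detectable difference or a larger sample.
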